### Intervention group

The Healthy Babies intervention consists of six in-home lessons taught by a trained paraprofessional instructor followed by three reinforcement telephone calls. Each lesson (60 minutes in length) is designed to promote the development of healthy infant eating and incorporates research-based information, opportunities for mothers to develop and practice skills, and a discussion of strategies to overcome challenges and problem-solving techniques. The three telephone contacts, about 5 minutes in length, made at 6, 8, and 10 months, are used to reinforce key concepts in the lessons after conclusion of the intervention to maintain effects and sustain contacts with participants to improve retention.

Six lessons have been identified as the number of lessons that best balance likelihood of completion by participants and likelihood of intervention impact. Six lessons have been found to produce behavioral change [14] and represent sufficient time to build a supportive relationship with the individual mothers.

During the six lessons, mothers will engage in activities in support of lesson goals. Intervention strategies focusing on feeding practices will include modification of the feeding environment (e.g., turning the TV off during feeding). An animated DVD, which includes actual footage of infant and parent behaviors, will be used to demonstrate infant temperament traits.

### Control group

The control group families receive the usual care provided by ENFEP. These families are newly enrolled into EFNEP as part of the HB study and have not received home visitation previously. The control lessons are delivered in a similar manner as the HB lessons, such that a paraprofessional instructor provides six lessons during an in-home visit, which each lesson lasting approximately 60 minutes. However, the control lessons focus solely on nutrition and the major food groups and do not include extensive content on infant-centered feeding. Paraprofessional instructors who provide the lessons for the control group families are different from the instructors who provide the HB lessons to prevent cross-contamination between the two groups.

### Procedures

Data are obtained by trained data collectors using various methods, including self-report questionnaires, anthropometric assessment, and videotaping of mealtime observations. All data collectors are trained to be as unobtrusive as possible when they are videotaping the mother-infant feeding interaction and to conduct data collections in an interactional style least likely to provoke social desirability characteristics on the part of the mother.

Data collection in both states occurs at baseline (prior to the first lesson), when the baby is 6 months old, and when the baby is 1 year old. The intervals for data collection were chosen to reflect points in time critical in determining outcomes, such as following the in-home learning and again, when the infant is 12 months old, determining sustainability. We expect that the follow-up (at 12 months of age) for mother-infant dyads during this critical developmental stage will be sufficient in measuring sustainability of change in maternal responsiveness, feeding style, and feeding practices.

To ensure consistency and accuracy of data collection and videotaping, a 2-day intensive training session is held for data collectors prior to the collection of data, followed by booster sessions in years 2 and 3. Training consists of a standardized training guide and protocol including review of the instruments, measurement of height/length and weight, and videotaping the mother-infant feeding interaction. Data collectors are monitored for quality and fidelity to the protocol on a quarterly basis. Weekly telephone contact and email communication also occur between the project manager and the data collector to facilitate open communication and fidelity to the protocol.

### Measures

#### Maternal outcomes

**Maternal responsiveness **is defined as the sensitive and accepting behaviors identified in a mother toward her infant. The Parent-Child Interaction Scale-Feeding (PCI-F) [15], formerly Nursing Child Assessment Feeding Scale (NCAFS) [15], consists of 76 binary (yes/no) scored observation items designed to assess the mother-infant interactions during a feeding interaction in the home. The PCI-F has well-documented reliability and validity; Cronbach's alphas for the subscales range from .60 to .83 [15]. The PCI-F has been used extensively in research studies globally. The feeding observation will be videotaped in the infant's natural setting with his mother.

**Feeding style **represents the mother's beliefs about and approach to controlling her infant's feeding behaviors. The Infant Feeding Styles Questionnaire (IFSQ) [16] is a maternal self-report instrument designed to measure maternal beliefs and feeding style behaviors. The IFSQ was pretested and validated with 150 African American first-time mothers with children ≤ 2 years of age. Reliabilities range from .75-.95 [16].

**Feeding practices **are maternal behaviors relating to what is fed and how often; they are essential for ensuring appropriate eating habits throughout childhood. The Infant Feeding Scale (IFS) is a 65-item food frequency scale we developed as an adaptation of the Harvard Service Food Frequency Scale for Children [17]. It consists of two subscales: (a) one identifies foods and beverages consumed by the infant, including number of times offered daily, average number of spoonfuls eaten, total food and liquid consumed in a 24-hour period, and frequency of foods eaten during a week; (b) the second consists of the feeding environment and states where the infant ate, what the infant was doing during mealtimes, whether the television was on, if the mother sat with the infant, what, if any, of the same foods did the mother eat, how frequently the infant was fed, when the infant was fed, and who fed the infant.

### Infant outcome

#### Infant growth pattern

Appropriate **i**nfant growth patterns are the rate of weight-for-length gain based on gender, age, type of feeding, and birth weight, such that an infant stays between the 5th and 84th percentile. Experts recently revised the terminology for childhood obesity, including infants, categorizing weight-for-length values above the 95th percentile as "overweight" and between the 85th and 95th percentile as "at-risk for overweight."

Infant growth pattern is the measurement of an infant's weight and length plotted over time using z scores. The infant's length and weight will be measured at all three times points to provide an objective measure of weight status. The infant is weighed in a clean diaper on an electronic scale, positioned in the center of the scale tray and weighed to the nearest half ounce. If the infant is too active, an alternative measurement technique is used where the parent stands on a scale and holds the infant. Infant length is measured in the recumbent position. These data will be entered into Epi Info V3.4.3 to calculate weight-for-length z scores. Digital scales will be calibrated at each home prior to weights being taken.

**Maternal knowledge and self-efficacy **are being assessed at all three time points using the Maternal Knowledge and Self-Efficacy scale we developed from a previous study [12] and adapted for this study. The self-report scale consists of 13 knowledge items (with an internal consistency of .73) and seven self-efficacy items (with an internal consistency of .94), takes approximately 5 minutes to complete, and has been used with lower-income mothers of infants [12].

### Maternal and infant conditions that may influence outcomes

Maternal depression and infant temperament are conditions that may impact the effectiveness of the intervention. Maternal and infant conditions will be assessed at the three time points. Maternal depression data will be collected using three questions from the Edinburgh Postnatal Depression Scale (EPDS-3) [18], which has an internal consistency of .8 [18]. Infant temperament will be assessed using the Revised Infant Behavior Questionnaire (IBQ-R) [19], a 47-item measure with internal reliability range of .73-.94. At baseline, we will also collect data on the mother's age, education, history of infant feeding, work status and occupation, ethnicity, marital status, number of adults in the home, and the presence of other adult caregivers (e.g., grandmother).

### Feasibility variables (process evaluation)

#### Mothers: recruitment, retention, and satisfaction

Participant eligibility information will be tracked by the supervisor for each county in both states for all participants approached and will be recorded on a recruitment chart and county recruitment form by the project manager (PM). The PM will track recruitment and attrition information for all participants enrolled in the study on a participant tracking form. Maternal satisfaction information will be assessed using the Maternal Satisfaction 5-item brief survey via a mailed-in postcard at the end of the lessons and by quarterly telephone calls to random participants made by an evaluator separate from the research team directly involved with delivering the intervention.

### Sample size, power calculations, and data analysis

#### Sample size and power calculations

A convenience sample of 394 mother-infant dyads (186 each per intervention and control group) is anticipated. Effect sizes were estimated from similar available data and are calculated to be conservative to avoid Type II errors. To assess differences in groups cross-sectionally, the maternal Nursing Child Assessment Satellite Training (NCAST) data were used with a reported an effect size *(d*) of .35. The minimal detectable effect size (MDES) with power of .80 with an alpha level of 5% for 2-tailed tests is .33 expressed as Cohen's d. Effect sizes exceeding .30 are deemed more likely to reach clinical significance. We used normative data from the NCAST database containing data from 431 African American women to provide examples of projected changes in outcomes that, if produced by the HB intervention, will be detected as statistically significant.

The MDES was calculated for the pair-wise group differences using an approach described by Rochon [20]. We used H3 type of hypothesis since the model contains group-by-time interaction, and the standardized MDES was approximately 0.4. That is, if the minimum difference between groups divided by the maximum standard deviation across two time points is equal to 0.4 or greater, then the treatment difference inconsistent over time will be detected as statistically significant with power .80 and alpha = .05 for 2-tailed tests. A 70% to 75% completion rate is typical for nutrition education. These factors have led us to propose a sample size for analysis by Time 3 of 278 mother-infant dyads, 139 per group after accounting for estimated attrition. Including oversampling to accommodate a conservative estimate of 25% attrition after 1 year, the final sample size to be enrolled is 372, 186 per group and per state (in each state, 93 mothers and infants will be recruited for each group).

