**Methods/Design:**

We will describe our study protocol for a multisite randomized control trial being conducted in Colorado and Michigan with an anticipated sample of 372 economically and educationally disadvantaged African American, Hispanic, and Caucasian mothers with infants. Participants are being recruited by county community agency staff. Participants are randomly assigned to the intervention or the control group. The intervention consists of six in-home visits by a trained paraprofessional instructor followed by three reinforcement telephone contacts when the baby is 6, 8, and 10 months old. Main maternal outcomes include a) maternal responsiveness, b) feeding style, and c) feeding practices. Main infant outcome is infant growth pattern. All measures occur at baseline and when the infant is 6 and 12 months old.

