## Methods/Design

### Overall study design

The design of this study is a randomized, experimental, short-term, longitudinal controlled trial (RCT) with a convenience sample of economically and educationally disadvantaged mothers of infants living in Colorado and Michigan. Participants are randomly assigned to the HB intervention or a control group with a goal of N = 139 participants per group by Time 3 data collection. There are three assessment periods: baseline (Time 1), when the infant is 6 months of age (Time 2), and when the infant is 12 months of age (Time 3). The United States Department of Agriculture (USDA) has funded this project for 3 years, making this multi-state collaboration between Michigan and Colorado possible.

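### The sample-size section opens with an enrolment of 394 dyads, which contradicts its own 186 per group and the 372 given everywhere else; 394 should read 372

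*Protocol article*

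**What the plan says.** The protocol article gives the enrolment total in three places.

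- The first sentence under *Sample size and power calculations*: "A convenience sample of 394 mother-infant dyads (186 each per intervention and control group) is anticipated".
- The last sentence of the same section: "the final sample size to be enrolled is 372, 186 per group and per state", with the split spelled out as "in each state, 93 mothers and infants will be recruited for each group".
- The Methods/Design paragraph of the abstract: "an anticipated sample of 372 economically and educationally disadvantaged African American, Hispanic, and Caucasian mothers with infants".

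The route to the enrolment figure is also given. The section proposes "a sample size for analysis by Time 3 of 278 mother-infant dyads, 139 per group after accounting for estimated attrition", and *Overall study design* repeats the same goal per group: "with a goal of N = 139 participants per group by Time 3 data collection". The step from the analysed to the enrolled number is "Including oversampling to accommodate a conservative estimate of 25% attrition after 1 year".

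The figure 394 appears once in the article.

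**The concern.** The total and the per-group number in the opening sentence cannot both be right under two groups of equal size. The gap is 22 dyads, too large to come from rounding. It also stands in the section that fixes the sample size, not in background text.

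What is at stake is the benchmark for recruitment. *Aims and Hypotheses* lists feasibility in a community setting among the hypotheses, and *Feasibility variables (process evaluation)* says that recruitment and attrition will be tracked. Those results will naturally be read against the planned enrolment. Enrolling 372 dyads is 100% of one printed total and 372/394 = 94.4% of the other.

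**Working it through.** **Inputs, all from the protocol article**

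- Analysed at Time 3: 139 per group, 278 in total (*Overall study design*; *Sample size and power calculations*).
- Attrition: 25% (*Sample size and power calculations*).
- Enrolled per group: 186. Enrolled per group and state: 93, in two states (same section).
- Enrolment totals: 394 (first sentence of that section); 372 (last sentence of that section, and abstract).
- Two-tailed alpha 0.05, power 0.80, detectable effect d = 0.33 (same section).

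**Step 1: reproduce the plan's own enrolment figure.** Enrolled = analysed / (1 − attrition).

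- Per group: 139 / 0.75 = 185.3, rounded up to 186. Two groups: 2 × 186 = 372.
- On the total: 278 / 0.75 = 370.7, rounded up to 371. The difference of one from 372 comes only from rounding within each group.

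So 372 follows from the stated inputs.

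**Step 2: check the split.** 93 × 2 groups × 2 states = 372, and 186 per state × 2 states = 372. Both agree with step 1.

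**Step 3: try to obtain 394.**

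- As a sum of two equal groups: 394 / 2 = 197 per group. The article does not give 197 anywhere.
- From 278 analysed: 1 − 278/394 = 0.294, that is 29.4% attrition. The article does not state this rate.
- With the mistaken inflation 278 × 1.25 = 347.5, rounded up to 348. This is not 394.
- With 30% attrition: 278 / 0.70 = 397.1, rounded up to 398 (199 per group). This is near 394 but not equal to it, and it fits neither the stated 25% nor the 186 per group.

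None of these calculations gives 394. It exceeds 372 by 394 − 372 = 22, and 22/372 = 5.9%.

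**Step 4: does the slip reach the power statement?** For a two-group comparison of means, the detectable effect is (1.960 + 0.842) × √(2/n).

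| n per group | Where it comes from | Detectable d |
|---|---|---|
| 139 | Time 3 goal | 0.336 (0.337 with the t distribution) |
| 186 | 372 enrolled | 0.291 |
| 197 | 394 enrolled | 0.282 |

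The stated 0.33 is close to the value for 139 per group and not to the value for 197. The cross-sectional power statement therefore does not use 394. The second detectable effect in the section, about 0.4 for the group-by-time model, cannot be re-derived because the within-subject correlation is not given; the present point does not depend on it.

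**The case against.** The best defence is that no careful reader would be misled. The article calls 372 final, derives it from stated inputs and repeats it in the abstract and the state split. The figure 394 is derived from nothing, is described only as anticipated, and is contradicted by the parenthesis that follows it. This defence stands as regards the weight of the point, but the printed number is still wrong.

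Two stronger readings are tempting.

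- A reader might infer that the trial has no single recruitment target, so that recruitment could stop at either number and be reported as planned. The article does not support this. Stopping at 394 would mean 197 per group, against the 186 per group in the same sentence and the 93 per group and state at the end of the section.
- A reader might infer that 394 reflects a second, heavier attrition assumption, because the section mentions a typical completion rate of 70% to 75% and 29.4% lies near the lower end. At 70% completion the totals would differ in effect: 372 × 0.70 = 260 completers against 394 × 0.70 = 276, with a goal of 278. But the article plans with one rate, 25%, and uses it to reach 372. A 30% rate gives 398, not 394. The origin of 394 cannot be settled from the text.

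**Conclusion.** The point holds as a minor correction of a stated sample size. The opening sentence is wrong by 22 dyads (5.9%), and the document's own figures identify 372 as the intended enrolment. The power statement, the Time 3 goal of 139 per group, the allocation and the analysis are unaffected. This rests on two groups of equal size and on the stated 25% attrition, both of which the article gives explicitly.

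**What to change.** In the first sentence of *Sample size and power calculations*, replace 394 with 372 and keep the 186 per group. All enrolment figures in the article then agree. Before doing so, the sponsor should confirm against the full protocol, which is not shown here, that 394 was never a deliberate target; if it was, the per-group and per-state numbers, the attrition rate and the abstract would need changing instead, with the reason stated. The cost is one number in one sentence, with no recalculation.

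### The group-by-time test is sized to detect about 0.4, above the only cited effect (d = .35), and its two time points are not named, so its fit to a sustained benefit is unclear

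*Protocol article*

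**What the plan says.** All the power figures stand in the article under Sample size and power calculations, and there are two sets.

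- **Cross-sectional.** The section names its source: "To assess differences in groups cross-sectionally, the maternal Nursing Child Assessment Satellite Training (NCAST) data were used with a reported an effect size". The value it gives is d = .35. For this comparison, "The minimal detectable effect size (MDES) with power of .80 with an alpha level of 5% for 2-tailed tests is .33 expressed as Cohen's d". On relevance, "Effect sizes exceeding .30 are deemed more likely to reach clinical significance".
- **Longitudinal.** "We used H3 type of hypothesis since the model contains group-by-time interaction, and the standardized MDES was approximately 0.4". The figure is explained by a condition on the standardised effect: "if the minimum difference between groups divided by the maximum standard deviation across two time points is equal to 0.4 or greater". When that condition is met, and with a two-sided alpha of .05, the section promises this result: "then the treatment difference inconsistent over time will be detected as statistically significant with power .80".

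The section then presents its considerations jointly as the basis for 139 dyads per group analysed at Time 3, and 186 per group enrolled after allowing for 25% attrition. It does not say which of the two tests decides efficacy. Data analysis says only that the primary analysis is by intention to treat, and that variables become covariates if the groups are seen to differ on them at baseline.

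Overall study design lists three assessments: baseline, 6 months and 12 months. Procedures gives the purpose of the last one: follow-up to 12 months "will be sufficient in measuring sustainability of change in maternal responsiveness, feeding style, and feeding practices".

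**The concern.** The only effect size the article cites, .35, and the .30 above which it expects clinical relevance both lie below what the longitudinal test can detect with 80% power. The section also says that effect sizes were set conservatively to avoid Type II errors, and 0.4 does not fit that intention if an effect near .35 is expected.

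The hypothesis behind the 0.4 is a second difficulty. It concerns a treatment difference that varies over time, while the 12-month visit is there to show that a benefit lasts. The text mentions two time points where the trial has three, and does not say which two.

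If this interaction were used to judge efficacy, a non-significant result could be read as failure although the intervention worked and its effect lasted.

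**Working it through.** **Inputs.** From Sample size and power calculations: two-sided alpha .05, power .80, 139 per group analysed, cited d = .35, relevance mark .30, detectable effects (MDES) .33 and about 0.4. The correlation r between two measurements of the same dyad is not given and is varied below. Normal approximation throughout, SD = 1; z sum = 1.960 + 0.842 = 2.802.

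**1. The cross-sectional figure is reproduced.**
MDES = 2.802 × √(2/139) = 0.336, against .33 stated. Power at .33 is 78.6%; exactly 80% at .33 would take 145 per group. The gap is within rounding.
Power at .35 = Φ(0.35/√(2/139) − 1.960) = Φ(0.958) = 83.1%. For 80% at .35, 129 per group would suffice.
Attrition: 139/0.75 = 185.3, so 186 per group, as stated.

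**2. The longitudinal figure, at face value.**
If 80% power is reached at 0.40, a one-degree-of-freedom test has power at d of Φ(2.802 × d/0.40 − 1.960):

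| d | Power |
|---|---|
| .40 | 80% |
| .35 | 68.8% |
| .33 | 63.7% |
| .30 | 55.6% |

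Rounding of the 0.4 matters little: at .35, an MDES of 0.395 gives 69.9% and one of 0.405 gives 67.8%. On this test, 80% at .35 would need 139 × (0.40/0.35)² = 181.6, so 182 analysed per group, or 182/0.75 = 243 enrolled per group, against 139 and 186 planned.

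**3. What the 0.4 implies, if it is a difference in change between two time points.**
MDES = 0.336 × √(2(1 − r)). Setting this to 0.40 gives r of about 0.29. Since r is not stated, power at .35 by assumed r is:

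| r | MDES | Power at .35 |
|---|---|---|
| 0 | 0.475 | 54% |
| 0.3 | 0.398 | 69% |
| 0.5 | 0.336 | 83% |
| 0.7 | 0.260 | 97% |

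**4. A fully sustained effect.**
- 6 and 12 months only: the group difference is .35 at both, so the interaction is .35 − .35 = 0 and power equals alpha, 5%.
- Baseline and one follow-up: the interaction is .35 − 0 = .35, and step 3 applies.
- All three visits (pattern 0, .35, .35; two-degree-of-freedom test, equal correlations): 72% at r = 0.3 and 86% at r = 0.5.

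**5. Baseline-adjusted difference at Time 3.**
MDES = 0.336 × √(1 − r²). At r = 0.29 this is 0.32, with 86% power at .35. At r = 0.5 it is 0.29, with 92% power. Because 1 − r² = (1 − r)(1 + r) is never more than 2(1 − r), this contrast is at least as efficient as the difference in change for any r.

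**The case against.** The strongest reply is that the section powers two comparisons, and that .35 was cited for the cross-sectional one, where it exceeds the detectable .33. That is correct. A reader might infer from the 0.4 that the trial does not deliver its stated 80% power. The article does not support this: it claims 80% for the interaction only at 0.4 or more, never at .35, and nothing makes the interaction the primary test.

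Putting .35 and 0.4 on one scale is also an assumption. It is a reasonable one, because 0.4 is itself defined as a group difference over a standard deviation and no other effect is offered, but the 69% depends on it.

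A reader might further infer that the test is built to miss a sustained benefit. That follows only if the two time points are 6 and 12 months, which the article does not say. With baseline as one of them, a lasting benefit is detected. The exact meaning of H3 lies in a cited source that is not at hand.

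Finally, baseline adjustment may be called a detail for the analysis plan, and r = 0.29 is obtained by assuming that 0.4 is a two-point difference in change. The second remark is fair: the gains in step 5 are illustrations. They may also not carry over to feeding practices, since infants enter before starting solids and food-intake items may vary little at baseline. On the first remark, the article does fix a rule, adjusting only when an imbalance is observed, and that rule can be improved.

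What the reply leaves standing is that one sample carries two detectable effects, one below and one above the only cited effect, with no statement of which test decides and no justification of 0.4.

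**Conclusion.** The concern holds for the longitudinal test and not for the trial's power as a whole. The cross-sectional comparison covers d = .35 with about 83% power. The group-by-time test, taken at its stated 0.4, has about 69% at .35 and 56% at .30, on the assumptions of a common effect scale and one degree of freedom. Whether it answers the sustainability question cannot be settled from the text: power for a fully sustained effect is 5% if the time points are 6 and 12 months, and about 69% if baseline is one of them and the 0.4 is taken at face value. Under either reading, a baseline-adjusted Time 3 difference addresses the aim more directly, and it is at least as efficient as a difference in change.

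**What to change.** - Name the efficacy contrast: the HB-minus-control difference at Time 3, with Time 2 supportive, from one longitudinal model on all randomised dyads.
- Adjust for the baseline score in every case where the outcome is measurable at baseline, instead of only when an imbalance is observed.
- Keep the group-by-time interaction as a secondary description of whether the effect changes, and name its time points.
- Replace the 0.4 statement with the MDES of the chosen contrast and its assumed correlation, for example about 0.32 at r = 0.29 or 0.29 at r = 0.5 (both correlations assumed). Alternatively, keep the statement and add that the interaction test has about 69% power at d = .35 on the same scale.

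The cost is rewording the sample size and data analysis paragraphs, before outcomes are analysed. The baseline, 6-month and 12-month data are already scheduled, and no participants or visits are added.

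### The 25% attrition allowance labelled conservative is the lowest loss in the plan's own 25–30% range, so 139 per group and the .33 detectable effect hold at best at one end of it

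*Protocol article*

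**What the plan says.** All of this is in the Protocol article, mostly under Sample size and power calculations.

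- Expected completion: "A 70% to 75% completion rate is typical for nutrition education".
- Target for analysis: "sample size for analysis by Time 3 of 278 mother-infant dyads, 139 per group after accounting for estimated attrition". Overall study design repeats it: "with a goal of N = 139 participants per group by Time 3 data collection".
- Inflation for loss: "Including oversampling to accommodate a conservative estimate of 25% attrition after 1 year", giving "the final sample size to be enrolled is 372, 186 per group and per state".
- Cross-sectional detectable effect: the MDES "with power of .80 with an alpha level of 5% for 2-tailed tests is .33 expressed as Cohen's d".
- Reference effect for the cross-sectional comparison: Nursing Child Assessment Satellite Training (NCAST) "data were used with a reported an effect size *(d*) of .35".
- Group-by-time comparison: a standardised MDES of about 0.4, also at 80% power and two-sided 5%.

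The completion rate is listed among the factors that led to the proposed sample size. No other basis for the 25% is given.

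**The concern.** For attrition, a conservative allowance plans for more loss than expected, or at least for the worse end of the expected range. Completion of 70% to 75% corresponds to attrition of 25% to 30%, so 25% is the favourable end. A reader told that the allowance is conservative will take 139 per group at Time 3, and the detectable effect tied to it, as protected. If the other end of the plan's own range occurs, neither figure is delivered as stated. At stake are the accuracy of the stated Time 3 sample and cross-sectional MDES, and the margin between that MDES and the reference effect of .35.

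**Working it through.** **Inputs** (Sample size and power calculations): 139 per group analysed; 186 per group enrolled; attrition 25% as used, and 30% as the complement of 70% completion; two-sided alpha .05; power .80; stated cross-sectional MDES .33; reference d = .35; group-by-time MDES about 0.4.

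**1. Reproduce the enrolment figure.** Enrolled = analysed/(1 − attrition): 139/0.75 = 185.3, rounded up to 186 per group, 372 in total. This matches the plan.

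**2. Slack at 25% attrition.** 186 × 0.75 = 139.5 per group. The target is met with half a dyad per group to spare.

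**3. Yield at 30% attrition.** 186 × 0.70 = 130.2, so 130 per group and 260 in total. That is 9 per group and 18 in total below the stated 139 and 278.

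**4. Cross-sectional MDES.** Normal approximation: MDES = (1.960 + 0.842) × √(2/n).

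- n = 139: 2.802 × √(2/139) = .336
- n = 130: 2.802 × √(2/130) = .348 (.3475 unrounded)

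The table adds the noncentral t values, which are used in the rest of this point.

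| Per group | Attrition | MDES, normal | MDES, noncentral t | Power at d = .33 | Power at d = .35 |
|---|---|---|---|---|---|
| 139 | 25% | .336 | .337 | 78.3% | 82.8% |
| 130 | 30% | .348 | .349 | 75.5% | 80.3% |

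The power columns use the noncentral t. The normal approximation, power = Φ(d√(n/2) − 1.960), gives 78.6% and 75.8% at .33, and 83.1% and 80.6% at .35.

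The stated .33 is thus already slightly low at 139 per group, where .337 rounds to .34. That part is rounding and is not due to attrition. The step due to attrition is .337 to .349, about .012.

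**5. Group-by-time MDES.** The 0.4 cannot be reproduced, because no within-subject correlation is given. If it is taken as exactly .40 at 139 per group and scaled by sample size, .40 × √(139/130) = .414, which still rounds to 0.4.

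**The case against.** The strongest reply has four parts.

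**The arithmetic is right and 25% is inside the range.** This stands. The inflation reproduces exactly, and at 75% completion, which the plan also calls typical, the goal of 139 is met. The fault lies in the label and in figures stated for one end only.

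**Completion may mean finishing lessons, not being measured at Time 3.** This stands in part. The rate is quoted for nutrition education, data collectors are separate from instructors, and the primary analysis is intent-to-treat, so a mother who misses lessons can still be measured. The reinforcement telephone calls are also meant to help retention, although they are described only for the intervention arm. On the other side, Time 3 is at 12 months of age and the lessons end before 6 months, which could mean more loss. The document does not settle this. It does use the completion rate as its basis for the sample size and offers no other. A reader might infer that 30% is the rate to plan on. The text does not establish that, and the point does not need it.

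**The effect is small.** This stands. The cost is about 2.5 to 3 percentage points of power, and the 80% target at d = .35 is still met with 130 per group. A reader might infer that both stated detectable effects fail at 30% attrition. Only the cross-sectional figure moves visibly, because .41 is still about 0.4. A reader might also work out power for the interaction at .35. The plan gives .35 only for the cross-sectional comparison, and the interaction effect is standardised differently, so that calculation has no basis in the document.

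**A larger enrolment of 394 is also mentioned.** The sentence reads "A convenience sample of 394 mother-infant dyads (186 each per intervention and control group) is anticipated". This does not help: 2 × 186 = 372, which is also the total in the Abstract and the stated final enrolment. Even 394 would leave 197 × 0.70 = 137.9 per group.

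**Conclusion.** The point holds as a minor correction. By the plan's own range, 25% is the lowest attrition and cannot be called conservative. Enrolling 186 per group delivers 139 only if attrition does not exceed about 25%. At 30% it delivers 130 per group, with a cross-sectional MDES of about .35, power of about 76% at d = .33, and power of 80% at d = .35 (down from 83%). What is lost is the margin over the reference effect, not the power target.

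This rests on two assumptions: that the quoted completion rate stands for Time 3 retention, as the sample size reasoning implies, and that the cross-sectional MDES is for a simple two-group comparison of means with equal groups. The second is supported by recovering .337 against the stated .33. The documents do not support reading this as an underpowered trial or as a need to enrol more dyads.

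**What to change.** Keep enrolment at 372. Under Sample size and power calculations, delete the word conservative and give the Time 3 sample and cross-sectional MDES at both ends of the range:

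- 25% attrition: 139 per group (278 in total), MDES .34
- 30% attrition: 130 per group (260 in total), MDES .35

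In Overall study design, note that the goal of 139 per group assumes 25% attrition. The group-by-time figure of about 0.4 can stay. If the quoted completion rate is not meant as Time 3 retention, say so and give the basis for 25%.

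The cost is a few words and slightly less favourable stated figures. Holding 139 per group at 30% attrition would instead need 139/0.70 = 198.6, so 199 per group or 398 in total, 26 more than 372. That is not needed to correct the text.
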